### Withdrawal of subject

Subjects may prematurely discontinue from the study at any time. Subjects must be withdrawn under the following circumstances:

- at their own request
- if the Investigator feels it would not be in the best interest of the subject to continue
- if the subject violates conditions laid out in the consent form / information sheet or disregards instructions by the study personal

In all cases, the reason why subjects are withdrawn must be recorded in detail in the CRF

Should the study be discontinued prematurely, all study materials (completed, partially completed and empty CRFs) will be retained.

### Additional study related procedures

Table 1 shows summarizes Study visits and Assessments.

### Laboratory testing

- SARS-CoV-2 spike protein and nucleocapsid antibodies at Visit 1, Visit 3, Visit 4, Visit 5, Visit 6 and Visit 7 (9ml blood)
- SARS-CoV-2 specific T- cell response at Visit 1 and Visit 3 (3x8 ml blood)

Antibodies will be measured by the Department of Laboratory Medicine using clinically validated ELISA tests (Roche, Switzerland). SARS-CoV-2 specific T-cell responses will be assessed by QuantiFERON assays with SARS-CoV-2 specific peptides at the research laboratory of the Division of Nephrology (Quiagen, Netherlands).

### Clinical data

- Baseline clinical data will be recorded at visit 1 (current medication including maintenance immunosuppression, medical history including date of transplantation) using the CRF document.
- Adverse events will be assessed at visits 2, 3, 4 and 5

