### 3. Background

Kidney transplant recipients are at high risk for a severe COVID-19 disease course and therefore prioritized to receive early vaccination against SARS-CoV-2 (1, 2). In general, the immune response to vaccination is reduced in immunosuppressed individuals including kidney transplant recipients. A recent study from Israel confirmed that only 37.5% of kidney transplant recipients developed detectable antibodies against the spike protein following full vaccination with BNT162b2 (Pfizer-BioNTech) (3). The type of maintenance immunosuppression may have a significant impact on the immune response in kidney transplant recipients. Patients treated with co-stimulation blockade (Belatacept) as maintenance immunosuppression showed even lower immunization rates of only 5.7 % (4).

Several strategies have been proposed to improve response to SARS-CoV-2 vaccination including additional dosing and mixing different vaccine types to broaden the presented antigen repertoire (heterologous vaccination or “mix-and-match strategy”) (5). Recent data show a higher reactogenicity of heterologous boosting in the general population (6). In the European Union there are currently two different classes of SARS-CoV-2 vaccines available: a) mRNA (mRNA-1273 [Moderna Biotech] and BNT162b2 [Pfizer-BioNTech]) and b) viral vector-based vaccines (ChAdOx1 [AstraZeneca] and Ad26COVS1 [Jansen]). Of these Ad26COVS1 is the only vaccine that has been shown to induce a protective immune response after a single dose (7). Kidney transplant recipients in Austria have primarily been vaccinated with mRNA-based vaccines.

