### Randomization

Randomization will be performed as soon as the SARS-CoV-2 antibody status is available.

- Patients included in the study will be randomized 1:1 to receive a third dose of the previously administered mRNA vaccine (mRNA-1273 or BNT162b2) or a single dose of Ad26COVS1
- Randomization will be stratified by the maintenance immunosuppressive regimen calcineurin inhibitor (CNI) vs co-stimulation blockade (Beletaccept)
- To ensure that comparison groups will be of approximately the same size a block randomization will be used in order to balance subjects randomized to each group (<https://www.meduniwien.ac.at/randomizer/>).

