## 8. Statistical analysis

### Sample size calculation

For testing the primary study endpoint (positive antibody to the SARS-CoV-2 vaccine) we assume a response rate of 30% and 50% in the mRNA and the viral vector-based vaccine treatment arms and expect a dropout rate of a maximum of 5%. Currently, no data on a third vaccination in kidney transplant recipients exist. The 30% response rate for the homologous vaccination group has been chosen expecting a slightly lower response rate to the third vaccination in kidney transplant recipients who did not respond to the standard 2-dose vaccination regime compared to the initial response rate of kidney transplant recipients to

the standard 2-dose vaccination regime (37% response rate). The 50% response rate estimate for the heterologous vaccination groups is based on early data from studies investigating heterologous vaccination which showed a higher reactogenicity after the heterologous vaccination. Enrollment of 100 patients per group will provide 80% power (alpha-error: 5%) to detect a difference in response between the two treatment groups.

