### Endpoint analysis

For all endpoints a per protocol analysis will be carried out.

For the primary endpoint (positive humoral immune response to SARS-CoV-2 vaccination at 4 weeks after the vaccination) SARS-CoV-2 S IgG antibody test results will be recorded and counts and percentages of patients exceeding the manufacturer defined cutoff of 0.8U/ml in each treatment arm will be reported. A chi-squared test will be employed to test for statistically significant differences in the number of responders (antibody concentration exceeds the manufacturer defined cutoff of 0.8U/ml) between the treatment arms.

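### The primary comparison is written as an unadjusted chi-squared test although baseline predictors are recorded and one is stratified on: a valid analysis, but a missed gain in precision

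*Protocol*

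**What the plan says.** - **Primary test** (Protocol section 8, Endpoint analysis): "A chi-squared test will be employed to test for statistically significant differences in the number of responders" between the arms. No stratum or covariate is named.
- **Randomisation** (section 6, Randomization): 1:1 in blocks, stratified by CNI versus belatacept. Arm 1 repeats the patient's earlier mRNA product, so that product must be known before treatment.
- **Baseline data** (section 6, Clinical data): "Baseline clinical data will be recorded at visit 1 (current medication including maintenance immunosuppression, medical history including date of transplantation"). Laboratory testing adds "SARS-CoV-2 specific T- cell response at Visit 1 and Visit 3 (3x8 ml blood"), and Table 1 agrees.
- **Prognosis** (section 3, Background): "The type of maintenance immunosuppression may have a significant impact on the immune response in kidney transplant recipients". The figures cited are 37.5% antibody response in kidney transplant recipients and 5.7% in those on belatacept, from two separate studies after standard vaccination.
- **Later stratification** (last paragraph of section 8): before any endpoint analysis, patients will be counted by immunosuppressant class and by initial vaccine. If the numbers are large enough, the analysis plan will be updated to add stratification. How large is not stated.
- **Sample size** (section 8): "we assume a response rate of 30% and 50% in the mRNA and the viral vector-based vaccine treatment arms", dropout of at most 5%, 100 enrolled per group, 80% power at an alpha of 5%.

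**The concern.** The protocol names a factor that it expects to influence response, balances the arms on it at randomisation, records it with other pre-treatment information, and then uses none of it in the primary comparison. Variation in response that baseline data could explain stays in the error term. The sample size leaves little to spare once the allowed dropout occurs, so any precision recovered from data already collected is worth having.

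The closing paragraph of section 8 only partly answers this. It covers immunosuppressant class and initial vaccine, not transplantation date or T-cell response. Whether and how to stratify is settled before endpoint analysis, which is not the same as before outcomes exist. Section 5 blinds only the patient, so nothing in the text prevents that decision being taken by people who can see arm and antibody result. Fixing the covariates now would close that gap as well as gain precision.

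**Working it through.** **Inputs from the protocol.** Response 30% and 50%; 100 enrolled per arm; dropout up to 5%, hence 95 evaluable per arm; alpha 5%. **Assumed:** a two-sided test without continuity correction, since the protocol states neither.

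**1. The plan's own figure.** Evaluable patients per arm:

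n = [1.960·√(2·0.4·0.6) + 0.842·√(0.3·0.7 + 0.5·0.5)]² / 0.20² = (1.358 + 0.571)² / 0.04 = 93.

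With 5% dropout, 93/0.95 = 98, against 100 planned. The figure reproduces.

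Power at 95 per arm: z = (0.20·√95 − 1.358)/0.678 = (1.949 − 1.358)/0.678 = 0.872, which gives 80.8%. With no dropout (100 per arm) power is 82.8%.

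**2. Effect of adjustment.** If baseline covariates explain a share R² of within-arm outcome variance, the adjusted comparison behaves approximately like an unadjusted one with 95/(1 − R²) patients per arm. The protocol does not give R², so a range is shown.

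| Assumed R² | Effective n per arm | Power | Evaluable n per arm for 80% |
|---|---|---|---|
| 0 | 95.0 | 80.8% | 93 |
| 0.02 | 96.9 | 81.6% | 92 |
| 0.05 | 100.0 | 82.8% | 89 |
| 0.10 | 105.6 | 84.8% | 84 |
| 0.15 | 111.8 | 86.8% | 80 |
| 0.20 | 118.8 | 88.7% | 75 |

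**3. Simulation checks at 95 per arm.**

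- Logistic regression with one continuous covariate, 6,000 runs per setting. Power of the adjusted test was 80.2%, 82.5% and 87.1% when the covariate explained 0, 5.4% and 16.9% of variance. The unadjusted test stayed between 80.1% and 81.0%. Type I error of the adjusted test was 4.5% to 4.9% in these settings, and 5.4% in a further one with 28.8% explained.
- Linear risk-difference model with two 50:50 covariates, 20,000 runs. Unadjusted versus adjusted power was 80.6% versus 80.8% when neither mattered, 81.0% versus 84.7% when each shifted response by 20 points, and 80.1% versus 86.2% for shifts of 30 and 20 points. In the last case the covariate variance is 0.25·0.30² + 0.25·0.20² = 0.0325. Against an average outcome variance of (0.21 + 0.25)/2 = 0.23, that is an R² of about 0.14.
- Weak covariates: two shifts of 10 points give 0.005/0.23, an R² of about 0.02. Adjusted power was 81.5% against 80.3%.

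**4. What the protocol's own prognostic figures give.** Apply the ratio 5.7/37.5 = 0.152 to belatacept patients, keep the arm rates at 30% and 50%, and assume a belatacept share, which the protocol does not give. For a share of 10%, control-arm rates are 0.300/(0.9 + 0.1·0.152) = 32.8% on CNI and 5.0% on belatacept. Explained variance is 0.1·0.9·0.278²/0.21 = 3.3%. The same steps in the vector arm give 7.7%. The average is 5.5%, and power is 83.0%. Shares of 2%, 5% and 20% give 81.2%, 81.9% and 85.6%. This gain comes from the randomisation stratum itself, not from the other baseline data.

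**5. Room for covariates.** Expected responders are 95·0.30 + 95·0.50 = 76. A model with arm, stratum, one regimen indicator and earlier product has 4 coefficients besides the intercept, or 76/4 = 19 responders each. Adding time since transplantation and T-cell response makes 6, or about 12.7 each.

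**The case against.** The strongest reply is that nothing is wrong. A chi-squared test is valid for a 1:1 randomised binary endpoint, it matches the sample-size basis, and the stated power reproduces. Preferring a more efficient estimator is advice rather than correction. This stands, and a reader who inferred an invalid test or an underpowered trial would go beyond the documents. Chance imbalance in baseline factors does not invalidate the randomised comparison either.

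Second, the unadjusted analysis is not final for every variable. The end of section 8 gives regimen class and earlier vaccine a conditional way in, and a separate analysis plan that is not available here may say more. This also stands. What remains is that the condition is undefined, its timing is tied to the analysis rather than to the outcome data, and two recorded variables lie outside it. The text does not show that the choice will be driven by results; it only fails to exclude that.

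Third, the evidence is thin for anything beyond the stratum. The figures in the Background contrast belatacept with recipients in general, in different studies, after two doses. This trial enrols only patients without antibodies after two doses, so even that contrast may not carry over. It is tempting to infer that transplantation date, baseline T-cell response or regimen differences among CNI patients are strong predictors. The protocol gives no figure for any of them, so the gain from adding them could be about one power point or none.

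**Conclusion.** The point holds as a missed efficiency gain, not as an error. The primary analysis as written ignores the stratum used at randomisation and the baseline data collected before treatment, and the clause on later stratification is too loose to make up for it. The planned power is met without adjustment (80.8% at 95 evaluable per arm). For an assumed R² of 0.02 to 0.20, adjustment would give 81.6% to 88.7%, a gain of about 1 to 8 percentage points. With uninformative covariates power is essentially unchanged and type I error stays near 5%. These figures assume a two-sided 5% test without continuity correction, the planned rates and 5% dropout. Where in the range the trial would fall cannot be read from the documents.

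**What to change.** In section 8, Endpoint analysis, make the primary analysis the covariate-standardised difference in response rates from a logistic model, with a 95% CI based on a robust or delta-method standard error. Specify, before any outcome is seen:

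- arm and the randomisation stratum (CNI versus belatacept);
- a simple coding of the visit 1 regimen, defined in advance and with few categories;
- the earlier mRNA product;
- optionally, time since transplantation (for example on the log scale) and visit 1 T-cell response;
- a simple rule for a missing baseline value;
- a fallback for a sparse stratum. With an assumed 5% belatacept share and the ratio in the working, about 0.6 responders would be expected among 9.5 such patients, so an ordinary logistic fit could fail. Penalised likelihood is one option.

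Keep the chi-squared test as a supporting analysis. Reword the last paragraph of section 8 to agree: either drop the later stratification, or give it a numerical threshold and a decision point before outcome data are available.

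Cost: a few sentences in the protocol or analysis plan and slightly more programming, with no new data, visits or patients. The main limit is that the list must stay short, given about 76 expected responders.

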### Benefit and risk assessment

Patients with immunosuppression are considered to be at great risk for a severe disease course of COVID-19 an additional vaccination will increase their chance to develop a protective immune response. The risk for adverse events following a third vaccination is low compared to the risk associated with a SARS-CoV-2 infection in this population. All study drugs have been approved by the European Medicines Agency (EMA).

## 7. Adverse event reporting

### Definitions

#### Adverse Events

An adverse event is by definition “any untoward medical occurrence in a patient or clinical investigation subject administered a pharmaceutical product and that does not necessarily have a causal relationship with this treatment.” (International Conference on Harmonisation [ICH] Guideline for Good Clinical Practice).

- Worsening of a pre-existing medical condition (e.g., cancer, diabetes, migraine headaches, gout) should be considered an adverse event if there is either an increase in severity, frequency, or duration of the condition or an association with significantly worse outcomes.
- Interventions for pretreatment conditions (e.g., elective surgery) or medical procedures that were planned before study enrollment are not considered adverse events.

The investigator is responsible for reviewing laboratory test results and determining whether an abnormal value in an individual study subject represents a change from values before the study. In general, abnormal laboratory findings without clinical significance (based on the investigator's judgment) should not be recorded as adverse events. However, laboratory value changes requiring therapy or adjustment in prior therapy are considered adverse events.

### Serious Adverse Events

A serious adverse event (SAE) is defined as an adverse event that:

- is fatal
- is life threatening (places the subject at immediate risk of death)
- requires in-patient hospitalization or prolongation of existing hospitalization
- results in persistent or significant disability/incapacity
- is a congenital anomaly/birth defect
- other significant medical hazard

A hospitalization meeting the regulatory definition for “serious” is any inpatient hospital admission that includes a minimum of an overnight stay in a health care facility. Any adverse event that does not meet one of the definitions of serious (e.g., emergency room visit, outpatient surgery, or requires urgent investigation) may be considered by the investigator to meet the “other significant medical hazard” criterion for classification as a serious adverse event. Examples include allergic bronchospasm, convulsions, and blood dyscrasias.

### Reporting procedures for all Adverse Events

The investigator is responsible for ensuring that all adverse events (as defined above) observed by the investigator or reported by subjects are properly captured in the subjects’ medical records.

In addition, the investigator is responsible for ensuring that, for those subjects randomized into the study, all adverse events captured on the subjects’ medical records (as specified

above) are reported on the case report form. This collection period will be from the time of administration of the study drug until the end of the study.

The following adverse event attributes must be assigned by the investigator:

- adverse event diagnosis or syndrome(s) (if known, signs or symptoms if not known)
- event description (with detail appropriate to the event)
- dates of onset and resolution
- severity
- assessment of relatedness to investigational product
- action taken

The relationship of the adverse event to the investigational product will be assessed by means of the question: “Is there a reasonable possibility that the event may have been caused by the investigational product?” The investigator should respond to this question with either Yes or No.

Medically significant adverse events considered related to the investigational product by the investigator will be followed until resolved or considered stable.

Adverse events will be reported in the publication arising from this study.

### [Serious Adverse Event reporting procedures](#)

Serious adverse events will be collected and recorded from the date the informed consent is signed through the end of the study. If a serious adverse event occurs before administration

of the investigation product, the relationship of the adverse event to study screening is to be assessed. If a subject is permanently withdrawn from treatment because of a serious adverse event, this information must be included in the initial or follow-up Serious Adverse Event Report Form as well as the Case Report Forms.

A SAE that is a known and previously described side effect of the treatment will be reported to the Austrian Federal Office for Safety in Health Care as well as the responsible ethics committee once a year in the form of a Development Safety Update Report (DSUR). Events that are suspected unexpected serious adverse reactions (SUSARs) will be reported to the responsible ethics committee and the European Medicines Agency. Fatal SUSARs will be reported as soon as possible, but latest within 7 days and non-fatal SUSARs within 15 days.

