#### COVID-19 Vaccine Moderna [mRNA-1273, Moderna]:

| System organ class                   | undesirable effect            | Frequency   |
|--------------------------------------|-------------------------------|-------------|
| Blood and lymphatic system disorders | Lymphadenopathy               | very common |
| Immune system disorders              | Anaphylaxis, Hypersensitivity | unknown     |

|                                                      |                                                                                 |                |
|------------------------------------------------------|---------------------------------------------------------------------------------|----------------|
| Nervous system disorders                             | Cephalaea                                                                       | very
common |
|                                                      | Acute Peripheral facial palsy                                                   | rare           |
| Gastrointestinal disorders                           | Nausea/Emesis                                                                   | very
common |
| Skin and subcutaneous tissue disorders               | Rash                                                                            | common         |
| Musculoskeletal and connective tissue disorders      | Myalgia, Arthralgia                                                             | very
common |
| General disorders and administration site conditions | Pain at Injection site, Tiredness, Chills, Fever, Swelling at injection site    | very
common |
|                                                      | Erythema at Injection site, Urticaria at injection site, Rash at injection site | common         |
|                                                      | Itching at injection site                                                       | uncommon       |
|                                                      | Facial swelling                                                                 | rare           |

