### Ethics and good clinical practice (GCP)

The Investigator will ensure that this study is conducted in full conformance with the principles of the "Declaration of Helsinki" (as amended at the 64th WMA General Assembly, Fortaleza, Brazil, 2013) and with the laws and regulations of the country in which the clinical research is conducted.

The Investigator of the clinical trial shall guarantee that only appropriately trained personnel will be involved in the study. All studies must follow the ICH GCP Guidelines and the regulatory requirements. Therefore, this study follows the EU Directive embedded in the Austrian drug act.

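### The 7-day SUSAR limit covers fatal cases only, so a life-threatening SUSAR that the patient survives falls under the 15-day limit

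*Protocol*

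**What the plan says.** Protocol section 7, under Serious Adverse Events, lists the criteria that make an event serious. Death is the first. The second is that the event "is life threatening (places the subject at immediate risk of death" (the closing bracket follows in the text). Hospitalization, disability, congenital anomaly and other significant medical hazards come after it.

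The section on serious adverse event reporting procedures then sets two routes:

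- **Known reactions.** "A SAE that is a known and previously described side effect of the treatment will be reported to the Austrian Federal Office", and to the ethics committee, "once a year in the form of a Development Safety Update Report (DSUR".
- **Unexpected reactions.** "Events that are suspected unexpected serious adverse reactions (SUSARs) will be reported to the responsible ethics committee and the European Medicines Agency". The deadlines follow: "Fatal SUSARs will be reported as soon as possible, but latest within 7 days and non-fatal SUSARs within 15 days".

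Section 10, under Ethics and good clinical practice, names the governing framework: "All studies must follow the ICH GCP Guidelines and the regulatory requirements. Therefore, this study follows the EU Directive embedded in the Austrian drug act". It prints no reporting deadline.

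**The concern.** The seriousness definition singles out patients at immediate risk of death. The reporting rule then sorts SUSARs by one question only: whether the patient died. A patient who nearly dies of an unexpected reaction and survives gets the same deadline as any other non-fatal SUSAR.

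What is at stake is how soon bodies outside the trial learn of a grave and unexpected event. Each patient receives a single dose, so outside notice can protect other participants only while some of them are still unvaccinated. The protocol shown describes no safety board and no stopping rule, and it gives no other deadline for expedited reports.

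**Working it through.** There is no figure of the plan to reproduce. The check sets the relevant texts side by side.

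**Step 1. Does the two-way split leave a gap?** No. Every SUSAR is either fatal or non-fatal, so every SUSAR has a stated deadline. This is an explicit rule, not a detail left open for another document.

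**Step 2. Where does a survived life-threatening SUSAR fall?**

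| Event | Class under the seriousness definition | Class under the reporting rule | Latest report |
|---|---|---|---|
| Fatal SUSAR | fatal | fatal | 7 days |
| Life-threatening SUSAR, patient survives | life-threatening, listed apart from fatal | non-fatal | 15 days |
| Other SUSAR, e.g. hospitalization | other serious | non-fatal | 15 days |

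The second row is the defect. The definition separates that event from the third row; the deadline does not.

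**Step 3. Does another section restore a shorter limit?** No. Life-threatening events are mentioned only in the definition of a serious adverse event. The general adverse event procedures, the benefit and risk assessment and the monitoring section set no deadline for them.

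**Step 4. Size.** Both inputs come from the reporting sentence: 15 days − 7 days = 8 days. This is the largest difference between the two limits. It assumes that both count from the same starting point, which the sentence does not state.

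**Step 5. The known-reaction route.** The sentence on annual reporting makes no exception for outcome, and fatal events are serious adverse events by definition. The summary of known risks lists anaphylaxis for all three vaccines, for example as "Anaphylaxis, Hypersensitivity" in the mRNA-1273 table, without reference to severity or outcome. The protocol does not say how expectedness is judged when a listed reaction ends in death. The text therefore leaves that question open; it does not settle it in favour of the annual report.

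**The case against.** **The benchmark is outside the protocol.** A reader might infer that the 15-day limit breaches the framework named in section 10. The documents do not support that inference, because they name the framework without printing its deadlines. Section 10 also binds the trial to the regulatory requirements, so if those are stricter, the stricter limit already applies and the defect is one of drafting. This stands, and it is why the point rests on the protocol's own two classes and its own 7-day limit. It does not remove the point: the reporting section is what site staff will work from, and it gives them 15 days in plain terms.

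**The annual route.** A reader might also infer that a fatal case of a listed reaction, such as fatal anaphylaxis, would be reported only once a year. That is one possible reading and no more. The rule covers effects that are both known and previously described. No risk table describes a fatal reaction, and the summary presents the tables as an overview, not as the reference for judging expectedness. A fatal case can equally be read as unexpected and due within 7 days. Only a request for clarification survives.

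**Practical consequence.** It is tempting to convert the delay into a number of further patients vaccinated. The documents do not allow this. They state no accrual period, nothing says reports will be made on the last permitted day, and no section links a report to a pause in vaccination. Moreover, the trial is single-centre and only the patient is blinded, so the investigators can know the event and the product at once. Only outside notification is late.

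**Rarity.** All three vaccines are approved and widely used, so few such events are to be expected among 200 patients. This lowers the priority, but it also makes the correction nearly free.

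**Conclusion.** The point holds in this form: the 7-day limit applies to fatal SUSARs only, and a life-threatening SUSAR that the patient survives has a 15-day limit, up to 8 days later, although the protocol recognises immediate risk of death as a class of its own. This follows from the protocol's wording alone and needs no outside source; the 8 days assume a common starting point for both limits.

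Neither a breach of the named regulations, nor a settled rule that fatal listed reactions wait for the annual report, nor any count of patients exposed in the interval is established. The matter concerns safety reporting only and touches no endpoint, test or sample-size figure. It should be fixed, as a cheap improvement to oversight, and is not a fundamental flaw.

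**What to change.** 1. In the section on serious adverse event reporting procedures, redraw the two classes: a SUSAR that is fatal or life-threatening is due as soon as possible and no later than 7 days; every other SUSAR is due no later than 15 days. Use life-threatening as section 7 already defines it.
2. Before finalising the sentence, check it against the framework named in section 10, since the protocol does not reproduce that text.
3. As a secondary clarification, add a sentence on how expectedness is judged when a listed reaction has a fatal outcome, and name the reference document for that judgement.

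The cost is two or three sentences in the protocol and a shorter deadline for a very small number of events. No dose, visit, endpoint or analysis changes.
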